### Schedule of events

#### Screening evaluation

Patients will be assessed using the MINI to assess current and lifetime depression and other psychiatric disorders, and will be used to verify psychiatric inclusion. The screening information based on the current episode, will be determined from the patient report and the records of a pre-study clinical assessment, conducted by a psychiatrist trained in TRD. The ATHF is a commonly used and reliable method of assessing the adequacy of prior antidepressant treatment [36, 37] and will be used to confirm eligibility based on inclusion criteria for treatment resistance. To address the potential for rater bias, whereby baseline scores are inflated to ensure patient eligibility [57], we will employ two separate depression rating scales, one to determine eligibility and a different scale to serve as the primary outcome measure [58]. As such, we will require a minimum severity of moderate depression on a separate measure, the patient health questionnaire (PHQ-9 > 9) [59], as an inclusion criterion. The Transcranial Magnetic Stimulation Adult Safety Screen (TASS) will be used to assess potential rTMS risk factors. A pre-study blood test that includes electrolytes, complete blood count, and thyroid stimulating hormone will be required to rule out any underlying medical causes of the depression. These results will be accepted if completed within the lesser of the current depressive episode or six months.

#### Clinical assessments during and after treatment

Clinical measures will be assessed the week before treatment and immediately after treatment completion (Friday, Visit 5), as well as at 1 and 4 weeks after treatment completion. The schedule of assessments is located in Table 1.

To compare results to other depression studies, we will examine depressive symptoms using clinician-rated and self-report scales. Secondary outcome measures will include the HRSD-6, SSI, the self-rated BDI-II, and the GAD-7. Female participants will also complete a complete reproductive history the week before treatment since the effects of high-frequency rTMS have been shown to vary based on circulating hormones [60].

**Table 1 Tab1:** Schedule of Assessments

Clinical Assessment Scales*	Screening and Baseline	Treatment Course 1		Follow-up Period 1			Treatment Course 2		Follow-up Period 2	
	Week 0	Visit 1,2, 3,4	Visit 5	Week 1	Week 4		Visit 1,2, 3,4	Visit 5	Week 1	Week 4
MINI	X									
TASS	X									
GAD-7	X		X	X	X			X	X	X
PHQ-9	X									
SSI	X		X	X	X			X	X	X
HRSD-17	X		X	X	X			X	X	X
HRSD-6	X		X	X	X			X	X	X
ATHF	X									
BDI-II	X	X	X	X	X		X	X		X
Side effect report	X	X	X	X	X		X	X	X	X
Reproductive history (females only)	X						X (prior to Visit 1 only)			
Substance Use Questions	X	X	X				X	X		
Stanford Expectancy Questionnaire	X						X (prior to Visit 1 only)			
HCS				X					X	
Group Assignment (participants and technicians)		X (after visit 1)		X	X					

MINI: Mini-International Neuropsychiatric Interview; TASS: Transcranial Magnetic Stimulation Adult Safety Screen; GAD-7: Generalized Anxiety Disorder 7-Item; PHQ-9: Patient Health Questionnaire 9-Item; SSI: Scale for Suicidal Ideation; HRSD-17: 17 Item Hamilton Rating Scale for Depression; HRSD-6: 6 Item Hamilton Rating Scale for Depression; ATHF: Antidepressant Treatment History Form; BDI-II: Beck Depression Inventory; HCS: Human Connections Scale

### Attendance and withdrawal criteria

Patients will be encouraged to attend all scheduled treatments. Those that meet the following criteria will be excluded from the per protocol analysis if they:

Miss / fail to attend any one of the five treatment days in the course overall.Miss / fail to attend more than five treatment sessions over the five days.Cannot tolerate stimulation of at least 90% RMT for the entire session on more than five treatment sessions.Develop active suicidal ideation with intent during the course of stimulation, or in the opinion of the site PI, that participation is not clinically indicated.Are admitted to hospital during the course of treatment.Withdraw consent to participate.

Patients will be discontinued if they experience worsening in depression, defined as an increase in HRSD-17 from a baseline of more than 25% at the post-treatment assessment or development of active suicidal intent or attempted suicide.

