## Methods

### Trial design and setting

Over three years, approximately 230 outpatients at CAMH and the University of British Columbia Hospital, meeting diagnostic criteria for MDD, will be recruited and randomized to a triple-blind sham-controlled trial (patient, rater and technician blinding). Combined, these two centres receive 600–800 referrals annually for psychiatric brain stimulation from nurse practitioners, family physicians and psychiatrists. At the CAMH site, referrals are received from across the province of Ontario for patients from all genders and across the adult lifespan. A similarly diverse population are referred to the UBC site, from metro Vancouver areas. We believe that this recruitment approach will lead to the inclusion of a wide range of patients with diverse backgrounds.

Patients will receive five consecutive days (Monday to Friday) of active or sham iTBS, administered eight times daily at 1-hour intervals, with each session delivering 600 pulses of iTBS over 3 min and 9 s. Sham treatments will be delivered using a shielded “sham coil” that reproduces auditory and tactile sensations of stimulation. Refer to Fig. 1 for a summary of the trial design.

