**Fig. 1 Fig1:**
[figure not shown]
Study flow chart

Following randomization, patients will undergo a series of assessments and motor threshold testing to determine the appropriate strength of stimulation. Depressive symptoms will be assessed using the Hamilton Depression Rating Scale (HRSD-17) [26]. The primary outcome analysis will include the change in HRSD scores from baseline to the end of the acute treatment. The HRSD-17 was selected to facilitate the comparison of outcomes in this trial to that of previous trials, since the HRSD has been standard in both rTMS and pharmacotherapy trials of patients with depression for decades [27–31]. The HRSD-6 [32], derived from the HRSD-17, will also be included as a secondary outcome measure. The Scale for Suicide Ideation (SSI) and self-report scales of depression and anxiety (Beck Depression Inventory, BDI-II and the General Anxiety Disorder, GAD-7), will also be completed. Side effects will be recorded at every visit and after every treatment session. Final assessments will be completed immediately after the last treatment. The one-week and four-week follow up assessments will be allowed within 1–2 days of the scheduled time points. Refer to Table 1 for a detailed schedule of assessments.

All treatments will be conducted with minimized personal contact (i.e., verbal communication) between the technician and patient to reduce the impact of nonspecific therapeutic contact on outcomes. The relevance of alliance extends beyond psychotherapy and has been shown to impact pharmacological interventions [33]. As a way to quantify the nonspecific active component of the treatment, a modified Human Connections Scale (HCS) will be administered following each treatment course (blinded and open label) to determine the impact of the patient’s sense of alliance with the technician on the therapeutic outcome [34]. This scale will be used as a secondary measure and explored with respect to its role in the treatment outcome.

Open Label: To ensure that all patients can receive a form of active treatment, those who have not achieved the response criterion (i.e., a 50% improvement from baseline on the HRSD-17) at the week four follow-up visit will be offered a second course of treatment, regardless of whether they initially received active or sham treatment.

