### Statistical methods

#### Clinical outcomes analysis

Primary Outcome Analysis: The primary outcome analysis on the change in HRSD-17 between baseline and end of treatment, will be conducted on an intention-to-treat basis. We plan to use multiple imputation methods developed by Schafer [62] to account for potential bias that may be incurred by missing data. Before the main effects analysis, descriptive statistics will be generated to summarize the data on all randomized participants to confirm that there are no group differences between the two conditions concerning baseline demographics and clinical characteristics. To assess for significant differences in treatment effects over time, a mixed-effects model with predictor variables for group (active vs. sham), time (baseline vs. end of treatment), and group-by-time interaction will be fitted to the data from the primary outcome measure (HRSD-17). The mixed-effects model will also be used to estimate the treatment effect over the full course of treatment.

Secondary Outcome Analyses: We will repeat the primary and secondary analyses in the same manner for the one-week post-treatment and four-week post-treatment time points. The same approach will be employed to assess treatment effects on the HRSD-6, SSI, BDI-II and GAD-7. Response and remission will be included as secondary clinical outcomes. Response will be defined as ≥ 50% reduction in symptoms on the primary outcome measure (HRSD-17) and remission will be defined as a post-treatment HRSD-17 < 8 [1]. We will use a conservative imputation that assumes non-remission or non-response if data is missing at the post-treatment assessment. A two-tailed Chi-squared test will assess the significance of any observed differences in the proportion of responders and remitters between groups based on pre- to post-treatment HRSD-17. Finally, we will summarize and compare the rates of adverse events, severe adverse events and dropouts in both groups.

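### The 25% worsening criterion cannot act during the five-day course, and what it discontinues is undefined; read as withdrawal, it conflicts with the open-label offer and creates outcome-dependent gaps at Weeks 1 and 4

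*Protocol article*

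**What the plan says.** - **The rule.** Attendance and withdrawal criteria: "Patients will be discontinued if they experience worsening in depression, defined as an increase in HRSD-17 from a baseline of more than 25" per cent, continuing "at the post-treatment assessment or development of active suicidal intent or attempted suicide". The sentence stands apart from the list of reasons for exclusion from the per-protocol analysis. It does not say what is discontinued.
- **The timing.** Clinical assessments during and after treatment places clinical measures in the week before treatment and "immediately after treatment completion (Friday, Visit 5), as well as at 1 and 4 weeks after treatment completion". The text under Fig. 1 agrees: "Final assessments will be completed immediately after the last treatment". Table 1 marks HRSD-17 at baseline, Visit 5, Week 1 and Week 4, with none at Visits 1 to 4. Of the depression outcome scales, only the BDI-II is taken on those days.
- **The course.** Trial design and setting: "Patients will receive five consecutive days (Monday to Friday) of active or sham iTBS". The second course follows the same assessment schedule.
- **The offer.** The Open Label paragraph under Fig. 1: "To ensure that all patients can receive a form of active treatment, those who have not achieved the response criterion" at Week 4 are offered a second course, whichever arm they were in. No exception is made for patients who worsened.
- **The analysis.** Clinical outcomes analysis fits a mixed model with time as baseline versus end of treatment and plans multiple imputation. For the later visits: "We will repeat the primary and secondary analyses in the same manner for the one-week post-treatment and four-week post-treatment time points".

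**The concern.** A criterion for stopping because of deterioration is normally tied to a measurement that can be taken while treatment continues. Here the triggering measurement follows the last session, so when the worsening limb first applies nothing is left of that course to stop. The word discontinued must then refer to something else, and the article does not say what.

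Two things depend on the answer. One is access to the second course, which the article says is there so that everyone can receive active treatment. A patient more than 25% above baseline at Visit 5 would have to reach a 50% improvement by Week 4 to fall outside that offer, so nearly all flagged patients belong to the group it is meant for. The other is completeness of the Week 1 and Week 4 data. If flagged patients leave the study, the worst Visit 5 outcomes are removed from both time points, and more of them from the arm that does worse.

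**Working it through.** **Step 1: the rule against the schedule.** The trigger is an HRSD-17 at the post-treatment assessment. That assessment is at Visit 5, after the last session, and no earlier repeat exists. The worsening limb therefore cannot stop any session of the course, and the same holds in course 2. The limb for suicidal intent or attempted suicide carries no such timing and can act during treatment.

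**Step 2: the possible meanings of discontinued.**

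- Stop the blinded course: empty, since none of it remains.
- No further study treatment: this removes the second course and conflicts with the Open Label paragraph. Week 1 and Week 4 data stay complete.
- Leave the study: the section heading points this way. It conflicts with the Open Label paragraph, because the offer is made at the Week 4 visit, and it removes Week 1 and Week 4 data.

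**Step 3: size, if the meaning is study exit.** From Sample size: post-treatment SD 8, pre-post correlation 0.27, difference 3 points. These reproduce the stated 105 per group: adjusted SD = 8 × √(1 − 0.27²) = 7.70, giving 104 per group by the normal approximation and 105 by the t-based calculation (two-sided 5% assumed).

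Assumptions not in the documents: baseline mean m of 20 or 23; baseline SD s of 4 or 6; sham mean change c of −4 to −8, with active 3 points lower; correlation of Visit 5 with Week 4 of 0.5 or 0.7; normal scores; Week 4 means equal to Visit 5 means; and Week 4 related to baseline only through Visit 5.

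A patient is flagged if Visit 5 > 1.25 × baseline. The quantity Visit 5 − 1.25 × baseline has mean c − 0.25m and variance 64 + 1.5625s² − 2 × 1.25 × 0.27 × 8 × s. For m = 23, s = 4, c = −4:

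- mean = −4 − 5.75 = −9.75 (sham), −12.75 (active)
- variance = 64 + 25 − 21.6 = 67.4, SD = 8.21
- flagged: Φ(−9.75/8.21) = 11.8% sham, Φ(−12.75/8.21) = 6.0% active

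The Week 4 difference was simulated with 1,000,000 patients per arm. Ranges run over the two Visit 5 to Week 4 correlations. Observed cases means the difference in mean change among unflagged patients.

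| m | s | c (sham) | Flagged sham / active | Observed cases | Imputed from baseline | Imputed from baseline and Visit 5 |
|---|---|---|---|---|---|---|
| 23 | 4 | −4 | 11.8% / 6.0% | 2.44–2.58 | 2.48–2.65 | 3.0 |
| 23 | 6 | −4 | 14.9% / 8.7% | 2.31–2.41 | 2.48–2.64 | 3.0 |
| 23 | 4 | −8 | 4.7% / 2.1% | 2.69–2.75 | 2.72–2.81 | 3.0 |
| 23 | 6 | −8 | 7.1% / 3.7% | 2.56–2.62 | 2.69–2.77 | 3.0 |
| 20 | 4 | −4 | 13.6% / 7.2% | 2.38–2.52 | 2.44–2.60 | 3.0 |
| 20 | 6 | −4 | 16.8% / 10.0% | 2.29–2.38 | 2.46–2.60 | 3.0 |
| 20 | 4 | −8 | 5.7% / 2.6% | 2.65–2.73 | 2.68–2.78 | 3.0 |
| 20 | 6 | −8 | 8.3% / 4.4% | 2.51–2.58 | 2.63–2.76 | 3.0 |

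A mixed model fitted only to baseline and Week 4 has the same information as imputation from baseline, so that column is also a guide to what such a model would return.

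**The case against.** The strongest reply is that the text establishes only an undefined word. A reader might infer that the rule cannot act on treatment at all and serves only to remove the worst patients from Week 1, Week 4 and the second course. The article does not support that. It nowhere says that a discontinued patient skips a visit or that safety follow-up ends, and barring the second course would itself be acting on treatment. The scope of discontinuation may be set out in the full protocol, which is not shown, and the rule could be meant as a safety exception to the open-label offer.

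A second reply is that observed-case figures describe an analysis the article does not plan. It plans multiple imputation, and because the rule depends on an observed Visit 5 score, imputation that uses this score removes the bias. The article does not say that the score is left out, and the contents of an imputation model are usual analysis-plan material. The flagged shares also depend heavily on the assumed sham response.

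Much of this stands, and the size is therefore stated only conditionally. Two things remain. The rule's threshold and timing are printed in the article and cannot operate during the course as its own schedule is written. And the only model described for Weeks 1 and 4, repeated in the same manner as baseline versus end of treatment, does not contain the Visit 5 score if taken literally.

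**Conclusion.** The worsening limb cannot act during the five-day course, and the article leaves open what it discontinues. Two of the available meanings, withdrawal and no further treatment, conflict with the open-label offer. Withdrawal also makes Week 1 and Week 4 data missing because of the Visit 5 outcome.

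The primary endpoint is unaffected, because the triggering score is itself the Visit 5 outcome. Response and remission at end of treatment are unaffected for the same reason.

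If flagged patients do leave the study, and under the assumptions listed, about 5–15% of sham and 2–9% of active patients are flagged at a baseline mean of 23, with upper ends of 17% and 10% at a mean of 20. A true 3.0-point Week 4 difference would appear as about 2.3–2.75 in observed cases and 2.4–2.8 with imputation from baseline alone. It stays at 3.0 when Visit 5 is used. The shrinkage is thus a risk that a small change removes, and not a demonstrated bias of the planned analysis. The point should be corrected, but it concerns secondary time points, follow-up of patients who worsened and access to the second course.

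**What to change.** 1. Reconcile Attendance and withdrawal criteria with Table 1, with Clinical assessments during and after treatment, and with the Open Label paragraph. State whether discontinued refers to treatment, assessments or the study, and how it bears on the offer of a second course. This review proposes no clinical rule.
2. State that meeting the criterion does not end the scheduled Week 1 and Week 4 HRSD-17, SSI and side-effect assessments, and that these data are analysed.
3. Analyse Visit 5, Week 1 and Week 4 in one longitudinal model, or include the Visit 5 HRSD-17 in the imputation for the later visits, in place of separate models of baseline against a single time point.

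The cost is a wording amendment and one line in the analysis specification. The visits are already in the schedule. The small downside is a few more follow-up contacts with patients who worsened.

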### Sample size

We will consider the 8 × 5 protocol successful if the active stimulation group achieves superior improvement (i.e., a larger reduction in the mean HRSD-17 score) versus sham on the HRSD-17. To detect the minimally clinically significant difference of three points [61] on the HRSD-17 with 80% power (based on post-treatment HRSD-17 standard deviation of 8 and pre-post correlation of 0.27 in the iTBS group in the THREE-D trial [19]), 105 patients per group are needed. We expect a low attrition of 10% given that the treatment course is only five days, increasing the number required to be randomized to 116 per group (232 in total).

### Statistical methods

#### Clinical outcomes analysis

Primary Outcome Analysis: The primary outcome analysis on the change in HRSD-17 between baseline and end of treatment, will be conducted on an intention-to-treat basis. We plan to use multiple imputation methods developed by Schafer [62] to account for potential bias that may be incurred by missing data. Before the main effects analysis, descriptive statistics will be generated to summarize the data on all randomized participants to confirm that there are no group differences between the two conditions concerning baseline demographics and clinical characteristics. To assess for significant differences in treatment effects over time, a mixed-effects model with predictor variables for group (active vs. sham), time (baseline vs. end of treatment), and group-by-time interaction will be fitted to the data from the primary outcome measure (HRSD-17). The mixed-effects model will also be used to estimate the treatment effect over the full course of treatment.

Secondary Outcome Analyses: We will repeat the primary and secondary analyses in the same manner for the one-week post-treatment and four-week post-treatment time points. The same approach will be employed to assess treatment effects on the HRSD-6, SSI, BDI-II and GAD-7. Response and remission will be included as secondary clinical outcomes. Response will be defined as ≥ 50% reduction in symptoms on the primary outcome measure (HRSD-17) and remission will be defined as a post-treatment HRSD-17 < 8 [1]. We will use a conservative imputation that assumes non-remission or non-response if data is missing at the post-treatment assessment. A two-tailed Chi-squared test will assess the significance of any observed differences in the proportion of responders and remitters between groups based on pre- to post-treatment HRSD-17. Finally, we will summarize and compare the rates of adverse events, severe adverse events and dropouts in both groups.

Exploratory Outcome Analyses: A multivariable regression model will be used to explore whether or not treatment resistance, patient expectancy, patient experience, or HCS modify the baseline adjusted treatment effect on the HRSD-17 (at day 5). The same analytic approach used for the primary outcome will be employed to assess for treatment effects on the HRSD-6, BDI-II, SSI and GAD-7. We will descriptively report the change from baseline to 5 days, 1-week, and 4-week post-treatment in the open-label 1 Hz right DLPFC phase and compare change, response, and remission in those who received active compared to sham stimulation in the blinded phase. Additionally, we will build a multiple regression model to explore how prior treatment condition, expectancy, and HCS score impact the baseline adjusted treatment effect in the open-label 1 Hz right DLPFC treatment group.

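### The 105 per group is sized for a baseline-adjusted comparison, but the primary model as written tests raw change, whose power is at best equal and otherwise lower by an amount that depends on an unstated baseline SD

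*Protocol article*

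**What the plan says.** The Sample size section of the protocol article sets the target and the inputs: "To detect the minimally clinically significant difference of three points" "on the HRSD-17 with 80% power", "based on post-treatment HRSD-17 standard deviation of 8 and pre-post correlation of 0.27 in the iTBS group" of an earlier trial. It arrives at 105 patients per group, raised to 116 for 10% attrition.

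The Primary Outcome Analysis (under Clinical outcomes analysis) takes the change in HRSD-17 from baseline to end of treatment, by intention to treat with multiple imputation. It states that "a mixed-effects model with predictor variables for group (active vs. sham), time (baseline vs. end of treatment), and group-by-time interaction will be fitted" to the HRSD-17 data. The same approach is carried to the one-week and four-week time points and to the HRSD-6, SSI, BDI-II and GAD-7.

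Baseline adjustment is named only in the Exploratory Outcome Analyses, which ask whether certain factors "modify the baseline adjusted treatment effect on the HRSD-17 (at day 5").

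**The concern.** A pre-post correlation can enter a sample-size calculation in two ways. If baseline is a covariate, the correlation reduces the variance of the post-treatment score to SD² × (1 − r²), which can only help. If baseline is subtracted, the variance becomes SD0² + SD1² − 2·r·SD0·SD1. With a correlation as low as 0.27, subtraction can add more noise than it removes.

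The sizing appears to use the first route and the analysis the second. If so, the single primary test does not rest on the variance that justified 105 per group. Its power for the 3-point difference may be below the stated 80%, and its confidence interval wider than the same data would allow. The secondary continuous analyses inherit the same form.

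**Working it through.** **Inputs.** From the Sample size section: difference 3; post-treatment SD1 = 8; correlation r = 0.27; power 80%; 105 evaluable per group. Alpha and sidedness are not stated for the primary test. I assume two-sided 0.05, which reproduces the stated figure. The only sidedness in the article belongs to the response and remission comparison ("A two-tailed Chi-squared test will assess the significance of any observed differences"). The baseline SD of the HRSD-17, SD0, is not given.

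**Step 1: reproduce 105.** ANCOVA variance = 64 × (1 − 0.27²) = 64 × 0.9271 = 59.33, so SD = 7.70. Normal approximation: n = 2 × (1.96 + 0.8416)² × 59.33 / 9 = 103.5, rounded up to 104. With the noncentral t distribution n = 105, and power at 105 is 80.2%. This matches the plan.

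Other calculations that use only the stated inputs do not match (noncentral t, two-sided, unless noted):
- post-treatment score alone, SD 8: 113 per group
- change score with SD 8 at both times: 164 per group
- one-sided 0.05, normal approximation: 82 (ANCOVA), 88 (post-treatment score), 129 (change score, equal SDs)

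A change-score calculation comes close to 105 only with an unstated baseline SD of roughly 2 to 3.

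**Step 2: what the stated model tests.** With two time points and terms for group, time and their interaction, the interaction is the difference between arms in mean change. This was checked on simulated complete data with baseline SD 5. The mixed model gave −3.898 (SE 1.136), and the direct comparison of change scores gave the same estimate and SE. ANCOVA on the same data had SE 1.049. Multiple imputation fills in missing values but does not alter this relation between the two analyses.

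**Step 3: compare the variances.**

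Change variance − ANCOVA variance = (64 + SD0² − 2·r·8·SD0) − 64·(1 − r²) = (SD0 − 8r)².

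With r = 0.27 this is (SD0 − 2.16)². It is never negative and is zero only at SD0 = 2.16. The direction therefore needs no assumption about SD0.

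**Step 4: size of the loss.** Change-score test, r = 0.27, SD1 = 8, 105 evaluable per group, noncentral t:

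| Assumed SD0 | Change variance | Power at 105 | n per group for 80% |
|---|---|---|---|
| 2.16 | 59.3 | 80.2% | 105 |
| 3 | 60.0 | 79.7% | 106 |
| 4 | 62.7 | 78.0% | 111 |
| 5 | 67.4 | 75.0% | 119 |
| 6 | 74.1 | 71.0% | 131 |
| 8 | 93.4 | 61.0% | 164 |

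ANCOVA power is 80.2% in every row.

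**Step 5: sensitivity to the correlation.** At r = 0.40 and SD0 = 5 the change variance is 64 + 25 − 32 = 57.0 and power is about 82%. At r = 0.54 and SD0 = 8 it is 64 + 64 − 69.12 = 58.9 and power is about 80%. ANCOVA in the same two cases would give about 84% and 89%.

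**The case against.** **The planned analysis is legitimate.** A change-score contrast in a randomised trial is unbiased with correct type I error, and the article frames success as greater improvement throughout. This stands: the point concerns power and precision, not validity.

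**The shortfall depends on a number the article does not give.** This also stands. Up to a baseline SD of about 4 the loss is roughly 2 points of power. The range in Step 4 also holds r at 0.27. The interval from baseline to the Friday assessment is short, so the true correlation may exceed the borrowed value, and a wider baseline spread would normally raise it. Step 5 shows that a shortfall below 80% is then not certain. What remains is that, on the inputs the plan itself chose, the stated test cannot beat the claimed power and in general falls short of it.

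**The model sentence is condensed, and the SAP may add a constraint.** This does not remove the point. The article lists the model's terms, with baseline as a level of time, and it lists the sizing inputs. The two do not match as stated, and a SAP that follows the article inherits the mismatch.

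**The attrition margin may cover it.** The step from 105 to 116 is already allotted to dropout. With no dropout at all, 116 evaluable per group would give 81.9% at baseline SD 4, 79.1% at 5 and 65.3% at 8.

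**Stronger readings that the document does not support.** A reader might infer that the primary and exploratory analyses pursue different effects because only the latter is called baseline adjusted. Under randomisation both estimate the same mean difference, and the exploratory regression contradicts nothing. A reader might also infer that a small baseline SD can be ruled out because entry severity is set on the PHQ-9. That only means there is no direct HRSD-17 cut-off. A PHQ-9 threshold can still narrow the HRSD-17 range indirectly, and the article does not show which baseline SD is plausible.

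**Conclusion.** The mismatch is real. The 105 per group for 80% power matches the ANCOVA variance, given the stated SD and correlation and an assumed two-sided 0.05. The primary model as written tests the difference in raw change. Under the same inputs that test is never more powerful than the sizing assumes, and equals it only at a baseline SD of about 2.2.

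The size of the loss is conditional on the unstated baseline SD: negligible at 3, about 2 points at 4, 5 at 5 and 9 at 6. It would be tempting to say that the trial has 61% power. That figure needs the value of 8, which the article labels as post-treatment, to apply at baseline too, and nothing in the article says so. A correlation above 0.27 would shrink the loss over the range considered.

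**What to change.** Make the primary analysis baseline-adjusted, in either of two ways:
- ANCOVA of end-of-treatment HRSD-17 on arm and baseline HRSD-17, after multiple imputation; or
- the same mixed model with a common baseline mean for the two arms, that is, without a group difference at baseline.

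Use the same form for week 1, week 4 and the secondary continuous scales (HRSD-6, SSI, BDI-II, GAD-7). The 105 per group then has the basis it was calculated on. The cost is one sentence in the protocol or SAP, with no extra patients or data and no change in the target effect. Settle it before unblinding, so that the choice between the two analyses cannot depend on the results.

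If the present model is kept, state the assumed baseline SD and its source, and restate the power (or the sample size) from the SD of change. In either case, state the alpha and sidedness used for the primary test.
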